### Randomisation

Randomisation will take place at the team level, to avoid contamination between the intervention and control groups. Before the inclusion of clients, participating teams will be randomly assigned to the GILL eHealth intervention or the control group providing care as usual. This procedure will be performed by a statistician blinded to the characteristics of the teams using a computer-generated list of numbers. To optimise comparability of the subgroups, treatment settings (FACT, assisted housing, long-stay wards) will be matched before randomisation. Blinding of clients and participating teams is not possible due to the nature of the intervention.

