#### Demographics

Demographic and clinical data (i.e., age, gender, ethnicity, marital status, educational level, employment status, psychiatric diagnoses, diagnoses of physical diseases, current smoking status) will be obtained at baseline to describe our sample, to control for possible confounders, to determine the MSSS, and to analyse the effects of sociodemographic situations on the results of the intervention.

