### Statistical analysis

Baseline data will be presented comparing the two treatment groups. Both intention-to-treat and per-protocol analysis will be conducted. To test the hypothesis that the tailored eHealth intervention will result in improved metabolic syndrome severity in SMI clients compared to usual care, linear mixed models will be used. The obtained betas describe the reduction in metabolic syndrome (Mets) Z score in the intervention group relative to the control group. Mixed-model analyses take the dependence of the repeated measurements into account, while using the maximum amount of information that is present in the data [49]. The main analyses will consist of fully corrected models. These models will be corrected for baseline values of the respective outcome plus include the covariates gender, age, and any other possible confounding variables on which the treatment groups differed at baseline. Also, ANCOVA will be used with the change of the Mets Z score (baseline – 12 months) as the outcome variable. Explanatory variables are gender, Mets Z score at baseline, and study group (intervention vs. control). The eHealth intervention succeeds if the lower mark of the two-sided 95% confidence interval is larger than zero. To test for within-group differences from baseline to the end of the intervention period, a repeated-measures ANOVA will be applied. The type-1 error is set to 5% (two-sided). For secondary outcomes, linear and logistic mixed models (depending on the outcome) will also be used to test the differences between the two groups. Missing values after 12 months will be conservatively replaced by the baseline-observation-carried-forward method to avoid an overestimation of the effect through dropouts.

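### The main model adds covariates according to observed baseline differences and does not name treatment setting, the one factor matched before randomisation

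*Protocol article*

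**What the plan says.** All references are to the protocol article.

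- **Statistical analysis, main model.** "The main analyses will consist of fully corrected models". These adjust for the baseline value of the outcome and "include the covariates gender, age, and any other possible confounding variables on which the treatment groups differed at baseline". No candidate list and no criterion for a difference is given.
- **Statistical analysis, ANCOVA of the 12-month change.** The list here is closed: "Explanatory variables are gender, Mets Z score at baseline, and study group (intervention vs. control"). Age, which is fixed in the mixed model, is absent, and so is setting.
- **Randomisation.** Teams are the unit of allocation, and "treatment settings (FACT, assisted housing, long-stay wards) will be matched before randomisation". No other matching factor is named.
- **Demographics.** Baseline demographic and clinical data are collected, among other purposes, "to control for possible confounders". Treatment setting is not among the items listed there or in Table 1.

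**The concern.** There are two linked problems.

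First, a rule that adds whatever differs between arms looks at the wrong property of a covariate. A strong predictor that happens to be balanced is left out, although adjusting for it would sharpen the estimate. A weak predictor that differs by chance is put in. The covariate set of the main analysis, and with it the estimate and interval, then depends on the realised baseline table.

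Second, the design used treatment setting to make the arms comparable, but the analysis does not name it. Setting could enter the main model only through the baseline-difference rule, and a factor matched in advance is one of the least likely to trigger that rule. If setting predicts the outcome, its variance stays in the error term and the standard error is larger than the matched design warrants.

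**Working it through.** **1. The plan's own sample size.** Inputs from the Sample size section: difference 0.40, power 0.80, alpha 0.05 (two-sided, from Statistical analysis), 10 teams per arm, ICC 0.01, dropout 15%. The SD is not stated; SD = 1 is assumed throughout.

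- Per arm before clustering: 2 × ((1.96 + 0.842)/0.40)² = 98.1 (plan: 98).
- With 10 teams per arm: 98 × (1 − 0.01)/(1 − 98 × 0.01/10) = 97.02/0.902 = 107.6 per arm, or 10.76 per team. Rounded up to 11 per team, this is 220 in total (plan: 220).
- Dropout: 220/0.85 = 258.8 (plan: 258).

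The chain reproduces to within rounding, and this point contests none of it.

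**2. How often chance alone adds a covariate.** Table 1 lists 10 baseline descriptors under demographics: age, gender, ethnicity, marital status, education, employment, psychiatric diagnoses, somatic diagnoses, smoking, and years in mental health care. Age and gender are already in the model, so 8 are open to selection. If a difference means p<0.05 and the 8 are independent, with no true imbalance:

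- P(at least one selected) = 1 − 0.95⁸ = 0.337, about 34%.
- For 5 or 10 candidates the figure is 23% or 40%.

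This is the chance that the model changes. It is not a bias or a type I error rate.

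**3. What omitting or including setting does to power.** The calculation is at team level, with 10 teams per arm and 11 clients per team. It ignores the baseline-score adjustment.

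- Variance of a team mean: 0.01 + 0.99/11 = 0.10.
- Standard error of the difference: √(2 × 0.10/10) = 0.1414. Noncentrality: 0.40/0.1414 = 2.828.
- Setting not in the model: 20 − 2 = 18 df, power 0.763.
- Setting in the model (three levels, two more parameters): 16 df. If it explains none of the between-team variance, power is 0.757.
- If it explains all of that variance, the team-mean variance falls to 0.09, the noncentrality is 0.40/√(2 × 0.09/10) = 2.981, and power is 0.80.
- Break-even: with 16 df, power returns to 0.763 when setting explains about 15% of the between-team variance.

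**4. Direction of the error when setting is omitted.** This was simulated with 20 teams of 11, teams split 10/6/4 over the three settings and balanced by arm (an assumption).

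| Scenario | Type I error, setting omitted | Power, setting omitted | Power, setting included |
|---|---|---|---|
| Total between-team variance 0.01, all due to setting | 0.038 | 0.77 | 0.80 |
| Setting SD 0.2 on top of the ICC | 0.021 | 0.62 | 0.76 |
| Setting SD 0.3 on top of the ICC | 0.009 | 0.44 | 0.75 |

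The last two rows add setting variance of 0.04 and 0.09, which exceeds what an ICC of 0.01 allows. They show what happens if the plan's ICC is too small, not what the plan's inputs imply.

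**The case against.** The best defence of the rule is that teams are randomised before clients are included, and the unblinded teams draw up the lists of eligible clients. Real imbalance is therefore possible and adjusting for it is reasonable. That stands as a reason to adjust, but the adjustment should be for prognostic factors named beforehand. The 34% figure describes only the case with no true imbalance.

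It can also be said that the article does not exclude setting and that stratification factors are often left to an analysis plan. For setting alone this has some force. It does not rescue the selection rule, which the article states positively and an analysis plan could repair only by departing from it.

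Several stronger readings are tempting but unsupported:

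- *The estimate can be chosen with the results in view.* The stated rule uses baseline data, not outcomes, and the article says nothing about whether analysts are blinded. Baseline outcome, age and gender are fixed, so the model is only partly data-driven.
- *Omitting setting biases the result or inflates false positives.* With balanced matching it does neither; the test becomes conservative.
- *The rule will always leave setting out.* Client numbers per team can vary and teams may be added, so setting could still differ between arms at client level. Selection is unlikely, not impossible.
- *The protocol shows that the settings differ strongly in metabolic risk.* The Background reports only higher mortality related to physical comorbidity in inpatients than in FACT clients. Adjustment for the baseline score would also absorb part of any difference in level.

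**Conclusion.** The point holds, with modest consequences. The main model is governed by a rule that selects on imbalance, and under the stated assumptions (5% tests, 8 independent candidates) chance alone would alter the model about one time in three. The only matching factor is missing from both named covariate lists.

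Within the plan's ICC of 0.01 and an assumed SD of 1, including setting changes power from 0.763 to somewhere between 0.757 and 0.80, so the most to be gained is about 4 points. A reader might infer that any prognostic value of setting repays the lost degrees of freedom; on these inputs it must explain about 15% of the between-team variance. The loss from omission is larger only if the true between-setting variance exceeds what the plan's ICC allows. The change should be made because it is cheap and makes the main model definite in advance, not because the trial is otherwise invalid.

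**What to change.** In Statistical analysis, replace the baseline-difference phrase with a closed list: baseline value of the outcome, age, gender and treatment setting (three levels). Because clients are recruited after teams are randomised, add by name any further prognostic confounders thought necessary, for example smoking status, before the arms are compared. Use the same list in the ANCOVA, which now lacks age and setting. Confine adjustment for observed baseline imbalances to a sensitivity analysis.

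The cost is a sentence or two of text and two team-level degrees of freedom. If setting turns out not to be prognostic, that is about 0.6 percentage points of power (0.763 to 0.757). Sample size and trial conduct do not change.

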#### Sample size

This RCT is powered to detect a mean difference of at least 0.40 in the metabolic syndrome severity Z score across 1 year between the intervention and control group. The mean difference in the metabolic syndrome severity Z score is estimated on the basis of earlier intervention studies [27, 45]. With a power set at 0.80, and an alpha of 0.05, two groups of 98 patients with SMI are needed in each group. Assuming an inclusion of 10 clusters (teams) within each arm, and assuming an ICC of 0.01 implies that 220 patients are required. Assuming a dropout rate of 15% [46, 47] and testing the intervention effect using two samples t-test, implies that we need to recruit a total of 258 patients. However, testing of the intervention effect by use of linear mixed models is likely to reduce bias and increase power [48].

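### Missing 12-month values are replaced by baseline without limit and the rule is called conservative, which it is not in general; it also undercuts the stated reason for the mixed model

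*Protocol article*

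**What the plan says.** All of this is in the protocol article. The primary outcome is the metabolic syndrome severity score at 12 months (Primary outcome). The score is also measured at 6 months (Table 1).

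The Statistical analysis section names a linear mixed model as the test of the main hypothesis and gives this reason: "Mixed-model analyses take the dependence of the repeated measurements into account, while using the maximum amount of information that is present in the data". The Sample size section adds that "testing of the intervention effect by use of linear mixed models is likely to reduce bias and increase power". A second analysis follows: "ANCOVA will be used with the change of the Mets Z score (baseline – 12 months) as the outcome variable". The success rule comes shortly after it: "The eHealth intervention succeeds if the lower mark of the two-sided 95% confidence interval is larger than zero".

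The section ends with the missing-data rule: "Missing values after 12 months will be conservatively replaced by the baseline-observation-carried-forward method to avoid an overestimation of the effect through dropouts". I read this as covering missing values at the 12-month visit. The article names no analysis or analysis set to which the rule is limited, and gives no other missing-data method.

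**The concern.** A client without a 12-month score is given the baseline score, so the recorded change is exactly zero. That is an assumption about the outcome, and the direction of its bias is not fixed. It pulls a real benefit toward zero. When clients in general get worse, however, it gives each dropout credit for not worsening, and the arm that loses more clients gains. Unequal loss is plausible here, since the trial is open and only one arm receives an added programme.

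The rule also works against the model. A likelihood-based mixed model uses a client's 6-month score, through the within-client correlation, to inform the missing 12-month score. Once baseline is written into that cell, the model takes it as observed and the 6-month score no longer informs it. At stake are the size of the primary estimate, the power to detect 0.40, and whether a positive result can be defended with the claim that the imputation could only have worked against it.

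**Working it through.** **Inputs from the article (Sample size).** Effect 0.40, two-sided alpha 0.05, power 0.80, 98 per arm, 10 teams per arm, ICC 0.01, 220 clients after clustering, 15% dropout with no split by arm, 258 in total.

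**Assumed.** SD 1 (none is stated, but the outcome is a Z score), the time trends, the dropout splits, and the baseline-to-12-month correlation.

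**1. The plan's own figures.**
- Per arm: 2 × (1.96 + 0.84)² / 0.40² ≈ 98.1 (stated: 98).
- Clustering with 11 clients per team: 1 + 10 × 0.01 = 1.10. Then 196 × 1.10 = 215.6, or 200 × 1.10 = 220 (stated: 220).
- Dropout: 220 / 0.85 = 258.8 (stated: 258).

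The figures reproduce to within rounding.

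**2. Expected estimate under baseline carried forward.** Let change be baseline minus 12 months, so that positive is better. Let μ be the mean change and d the dropout in each arm (I intervention, C control), with dropout unrelated to outcome. Then

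estimate = (1 − d_I) × μ_I − (1 − d_C) × μ_C.

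| Case | μ_I, μ_C | d_I, d_C | True effect | Estimate |
|---|---|---|---|---|
| Design values | 0.40, 0 | 15%, 15% | 0.40 | 0.85 × 0.40 = 0.34 |
| No effect, no trend | 0, 0 | any | 0 | 0 |
| Worsening 0.2 | −0.2, −0.2 | 20%, 10% | 0 | −0.16 + 0.18 = +0.02 |
| Worsening 0.3 | −0.3, −0.3 | 20%, 10% | 0 | −0.24 + 0.27 = +0.03 |
| Worsening 0.3 | −0.3, −0.3 | 10%, 20% | 0 | −0.27 + 0.24 = −0.03 |
| Improvement 0.3 | 0.3, 0.3 | 10%, 20% | 0 | 0.27 − 0.24 = +0.03 |
| Worsening 0.3, extreme split | −0.3, −0.3 | 25%, 5% | 0 | −0.225 + 0.285 = +0.06 |

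The sign follows the trend and the dropout difference.

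**3. Power under the protocol's t-test and design effect, SD 1 for the 12-month score.**
- Observed data: 0.85 × 129 = 109.65 per arm. Design effect 1 + 9.965 × 0.01 ≈ 1.100, so effective n is 99.7. SE = √(2/99.7) = 0.142; 0.40/0.142 = 2.82; power 0.81.
- Baseline carried forward: 129 per arm. Design effect 1 + 11.9 × 0.01 = 1.119, so effective n is 115.3. SE = √(2/115.3) = 0.132; 0.34/0.132 = 2.58; power 0.73.

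**4. Simulated ANCOVA of change at the design values** (129 per arm, 4,000 runs, correlation 0.7, no clustering). Baseline carried forward: estimate 0.340, SE 0.084. Observed data: 0.400, SE 0.097. No dropout at all: SE 0.089. The imputed analysis therefore reports more precision than a trial with no missing data, because the zeros count as observations.

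**5. False success with no true effect** (same simulation, correlations 0.5 to 0.8, nominal 2.5% in the favourable direction). At worsening 0.3 with 20% vs 10% dropout it is about 5 to 6%.

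**The case against.** **The stated aim is reasonable, and sometimes met.** With equal dropout and a real benefit the bias is toward zero, and with no effect and no trend there is none. If intervention dropouts would have gained nothing, the effect over all randomised clients is 0.85 × 0.40 = 0.34. Baseline carried forward then returns that value, while completers give 0.40. This stands. The 15% dilution is an error only if dropouts would have kept the benefit. It shows that the rule can be conservative, not that it always is.

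**The power loss depends on the analysis.** This also stands. The 0.73 is for a t-test on the 12-month score. If SD 1 is read as the SD of change, the zeros shrink it to about 0.93, and 0.34/(0.93 × 0.132) ≈ 2.8 gives power of about 0.80. In the baseline-adjusted simulation the signal is nearly unchanged: 0.34/0.084 = 4.05 against 0.40/0.097 = 4.12. The diluted estimate remains in each case.

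**Scope is open.** The section lists several analyses and does not say which one the rule serves. The analysis plan is not shown and might confine it. As written there is no limit. Restricting it to the ANCOVA would still leave zero changes in the analysis that the success rule follows.

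**Stronger readings that a reader might infer, but which are not supported:**
- *The method understates its own variance.* In simulation the model SE (0.084) matches the actual spread of the imputed estimator (0.085). The point is only that invented values add apparent information.
- *It contradicts the sample size.* Inflating for lost clients and later imputing them is a cautious convention, not a contradiction.
- *The 6-month data are discarded.* An observed 6-month score still enters the repeated-measures model as an outcome. It only stops informing that client's month 12.
- *The type 1 error will double.* One simulation (20 teams of 13, ICC 0.01, correlation 0.7) gave 10.1% two-sided rejection against 5.1% for observed data. That needs 25% vs 5% dropout together with worsening of 0.3, and the article gives neither. It is an extreme assumed scenario.

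**Conclusion.** The point holds in this form. The article applies baseline carried forward to the 12-month primary outcome without limit and calls it conservative, and that description is not true in general.

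- **Dilution:** a true 0.40 becomes 0.34 at the protocol's own 15% dropout, if dropouts would have had the same effect as completers. Power under the protocol's t-test and design effect is then about 0.73 instead of 0.80, with SD 1 assumed for the 12-month score. The loss is small in a baseline-adjusted analysis.
- **Bias toward the intervention:** with no true effect it is 0.02 to 0.03 at 20% vs 10% dropout and worsening of 0.2 to 0.3, and 0.06 at 25% vs 5% and worsening of 0.3. Trends and splits are assumed. Reversing either the trend or the split reverses the sign.
- **Inconsistency:** the mixed model was chosen for "while using the maximum amount of information that is present in the data", and the rule prevents this for any client seen at 6 months but not at 12.

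**What to change.** - Make the primary analysis the likelihood-based mixed model fitted to all observed 6- and 12-month scores of all randomised clients, with no baseline carried forward. It is valid if data are missing at random given the observed scores and covariates.
- Keep baseline carried forward at most as a labelled sensitivity analysis, and name the analysis to which it applies.
- Place beside it one sensitivity analysis that allows data not missing at random. Multiple imputation with a delta shift by arm is one option among several.
- Delete *conservatively*.

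The cost is a change of wording and one extra sensitivity analysis, with no new data. The downside is that the primary estimate then relies on missing at random, which is why the added sensitivity analysis is needed.

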### Analysis process evaluation

To objectify the process evaluation, interviews will be audio recorded, transcribed verbatim for analysis. MAXQDA software will be used for coding and structuring themes, following methodology of thematic analysis [50]. To systematically evaluate aspects of implementation, questions based on the RE-AIM model [51] will be added. RE-AIM assesses five dimensions of the implementation: reach, effectiveness, adoption, implementation, and maintenance. The process of data collection and analysis is iterative, meaning that the researchers will start data analysis after the first interviews to further explore and validate emerging themes in the next interviews.

## Discussion

Limited eHealth-supported lifestyle interventions are available for clients with SMI, tailored to their specific needs and characteristics. However, given the overall burden of poor physical health on clients with SMI [7], there is an urgent need for systematic somatic screening and effective lifestyle interventions. This paper presents the design of the GILL eHealth intervention. This cluster RCT will provide new information on the effects of systematic somatic screening and lifestyle promotion on physical health in clients with SMI. It also gives new insights on the use of eHealth in this population. The process evaluation will lead to the development of an implementation guide. This might provide additional information on the implementation of eHealth programmes, which could be used for broad implementation of GILL eHealth and future eHealth modules.

A strength of this study is its pragmatic design. The study will be conducted in mental health teams and implemented as part of essential care. In this way clients, treatments, and procedures resemble daily clinical practice. This increases the generalisability of the study outcomes. Another way the generalisability is enhanced is by including clients with SMI who receive care within different treatment settings. This limits the treatment setting as influencing factor on effectiveness and implementation. An additional strength is the quality of the GILL eHealth intervention. GILL eHealth is the result of a long-term development trajectory and is adapted to the preferences of clients and nurses. The intervention is based on current national and international guidelines [19]. It is therefore a realistic assumption that the GILL eHealth intervention will be more effective than usual care in improving physical health and lifestyle behaviours.

The GILL eHealth intervention does not allow for blinding of participants and nurses for the study. However, this reflects the daily practice and matches the pragmatic study design. Most important is to prevent contamination between the two study conditions – therefore the cluster-randomised design will be applied, in which the nurses working in the usual care teams will not receive training.

The underlying reasons that stall the implementation of systematic somatic screening and lifestyle interventions could become a limitation in this study. Currently only 17% of clients with a psychotic disorder in the Netherlands receive systematic somatic screening [52], even though it is considered essential care. Nurses have a crucial role in implementing somatic screening and lifestyle plans, yet experience this as challenging because they feel they lack skills and sufficient tools to perform the tasks [53]. Additionally, it is not always clear which tasks are the responsibility of nurses or nurse practitioners, and how multidisciplinary collaboration within and outside mental health care can be organised most effectively [54–56]. For this study an implementation group will be formed, to enhance implementation and dissemination. The nurses will also be trained in providing the eHealth, fulfilling their reported needs for training [57, 58]. GILL eHealth will offer structure in the somatic screening, supporting nurses in performing their tasks as care manager and giving a clear overview of the tasks involved.

Overall, this study will yield important and relevant information on the use of eHealth modules for improving physical health and lifestyle behaviours. The GILL eHealth module can become a clinically relevant tool when proven effective. This study will also provide insight into the barriers and facilitators for effective implementation. The first study results are expected in 2025.

